### Participant timeline

We will conduct the feasibility study over a 36-month period. Participation in the study and interventions will occur in the first 30 months.

### Sample size

We plan to enroll 20 neonates with gastroschisis from the University of California Davis (UCD) and the University of California Los Angeles (UCLA). This sample size was determined based on availability and feasibility. We estimate that approximately 10 neonates per year will meet the eligibility criteria, yielding a denominator of approximately 40 for the consent outcome (feasibility objective 1) and that the number of enrolled patients will be at least 20 for the proportions used for feasibility objectives 2 to 4. These two denominators will allow us to estimate these proportions with error margins less than 16 and 22 percentage points, respectively.

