### Outcomes

#### Feasibility objective outcomes

We will test the feasibility of implementing an early feeding protocol for neonates with gastroschisis. Feasibility will be assessed through:Objective 1 Enrollment (primary feasibility objective): obtain consent from ≥ 80% of eligible neonates’ parents/guardians from the prenatal period to within the first 24 h of abdominal closure.Objective 2 Protocol adherence: ≥ 85% of enrolled neonates receive introductory feeds within 48 h of abdominal closure.Objective 3 Fidelity: feeding protocol adherence with ≥ 90% of predefined protocol steps.Objective 4 Withdrawal: < 10% of enrolled neonates withdraw.

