## Trial status

IRB Protocol Version Date is January 31, 2025. Recruitment started February 20, 2025. The anticipated date of recruitment completion is February 1, 2028. Registered March 10, 2025 retrospectively registered.

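### The consent denominator of about 40 does not follow from 10 eligible neonates per year over any stated recruitment window, so the worst-case margin of under 16 points for the primary objective is unsupported

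*Protocol article*

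**What the plan says.** All references are to the protocol article.

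- **Sample size**, planned enrolment: "We plan to enroll 20 neonates with gastroschisis", from the two sites named together.
- **Sample size**, eligible pool: "We estimate that approximately 10 neonates per year will meet the eligibility criteria, yielding a denominator of approximately 40 for the consent outcome". The same sentence expects no fewer than 20 enrolled as the denominator for objectives 2 to 4.
- **Sample size**, precision: the two denominators are said to give "error margins less than 16 and 22 percentage points, respectively".
- **Feasibility objective outcomes**, objective 1: "Enrollment (primary feasibility objective): obtain consent from" at least 80% of the parents or guardians of eligible neonates.
- **Participant timeline**: the study lasts 36 months, and "Participation in the study and interventions will occur in the first 30 months". The Methods paragraph of the Abstract also gives 30 months for enrolment.
- **Trial status**: recruitment opened on 20 February 2025, and "The anticipated date of recruitment completion is February 1, 2028".
- **Statistical methods for primary and secondary outcomes**: each feasibility proportion is reported with a 95% confidence interval.

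**The concern.** The Sample size section presents 40 as a consequence of the yearly eligible rate, so it should equal that rate times the length of recruitment. It does not. The number matters because objective 1 is the primary feasibility objective, and this sentence is the article's only statement of how precisely it will be estimated. If the denominator is too large, the stated margin is too small.

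There are two further tensions. The 30-month window and the recruitment dates do not agree, and the denominator depends on which applies. Also, 20 enrolled, 40 eligible and a consent target of at least 80% do not sit together comfortably.

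**Working it through.** **1. Reproduce the stated margins.** The 95% half-width for a proportion is 1.96 × √(p(1 − p)/n), largest at p = 0.5.

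- n = 40, p = 0.5: 1.96 × √(0.25/40) = 15.5 points (stated: under 16).
- n = 20, p = 0.5: 1.96 × √(0.25/20) = 21.9 points (stated: under 22).

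Both match. At p = 0.8, n = 20 would give 17.5 points, so the paired 22-point figure shows that the worst case was used. The margin arithmetic is right for n = 40; the question is whether 40 is right.

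**2. Derive the denominator.** Eligible = yearly rate × years of recruitment.

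| Window | Source | 10 per year in total | 10 per year at each site |
|---|---|---|---|
| 30 months (2.5 years) | Abstract; Participant timeline | 25 | 50 |
| 20 Feb 2025 to 1 Feb 2028: 1,076 days, 2.95 years, 35.4 months | Trial status | 29.5 | 59 |
| 36 months (3 years) | Participant timeline, whole study | 30 | 60 |

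No cell gives 40. A total of 10 per year would need 48 months. A per-site rate would need 24 months. The article states neither.

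**3. Recompute the objective 1 margin on the same basis.**

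| n | Half-width at p = 0.5 | Half-width at p = 0.8 |
|---|---|---|
| 25 | 19.6 | 15.7 |
| 30 | 17.9 | 14.3 |
| 40 | 15.5 | 12.4 |

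A worst-case bound of 16 points requires n ≥ 0.25 × (1.96/0.16)² = 37.5, so at least 38.

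**4. Compare the planned sizes with the consent target.**

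- 20/40 = 50%, against a target of at least 80%.
- 0.80 × 40 = 32 enrolled, against a plan of 20.
- 0.80 × 25 = 20, so 25 eligible, 20 enrolled and 80% consent agree with each other and with 10 per year over 30 months.

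**5. Consequence for objectives 2 to 4.** The 22-point margin needs 20 enrolled: 0.25 × (1.96/0.22)² = 19.8. With 25 eligible and 80% consent, expected enrolment is exactly 20, which leaves no slack. On the Trial status dates it is 0.80 × 29.5 = 23.6. The margin is therefore conditional on reaching 20.

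**The case against.** The strongest reply is that little depends on this figure. The sample size was set by availability and feasibility, no efficacy hypothesis is tested, and the final intervals will use whatever denominators are observed. If consent is at the 80% target, the half-width at 25 to 30 eligible is under 16 points anyway. All of that is true, and it limits the consequence. It does not rescue the sentence, which states the bound without conditions and on a worst-case basis. Nor can an approximate figure absorb the gap, since 40 exceeds the derived values by 33% (40/30) to 60% (40/25).

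A reader might infer more than the article supports:

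- *That the trial plans for 50% consent and so expects to fail its primary criterion.* The article states no such rate. It treats 20 as a floor for enrolment as well as a plan, and 32 of 40 would satisfy both the floor and the target. Some tension remains, because the section plans for 20, Recruitment refers to a target sample size, and the data reviews end at ten completers per site.
- *That the precision is missed at every consent rate.* It is missed as a guaranteed bound, not at 80% consent.
- *That 25 is the only denominator that fits, so 40 must be the error.* The target is at least 80%, so any denominator from 20 to 25 fits 20 enrolled. The error could lie in the rate, the window or the 40.
- *That 20 enrolled is unlikely to be reached.* That depends on the window, on an assumed accrual model and on the consent rate. The article also plans additional outreach to reach its target.

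**Conclusion.** The point holds as an inconsistency in the Sample size section. The consent denominator of about 40 cannot be obtained from about 10 eligible neonates per year over 30, 35.4 or 36 months, whether the rate is total or per site. If the rate is a total, which is the natural reading because the two sites are named together just before it, the denominator is 25 to 30. The worst-case 95% margin for the primary objective is then 19.6 to 17.9 points instead of under 16, a loss of 2.4 to 4.1 points against the 15.5 that n = 40 gives.

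This rests on constant accrual at the stated rate and on the normal-approximation half-width that reproduces both published margins. The article shows that rate, window, denominator, planned enrolment and consent target do not fit together as written. It does not show which of them is wrong.

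**What to change.** Reconcile four quantities and state each once: the eligible rate (saying whether it is for both sites together or per site), the recruitment window (30 months, or to 1 February 2028), the consent denominator, and the planned enrolment. Then recompute the objective 1 margin from the reconciled denominator.

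If 10 per year in total over 30 months is kept, the section could read: *About 10 eligible neonates per year across both sites over 30 months gives about 25 eligible. At 80% consent, about 20 would be enrolled. The worst-case 95% margin is under 20 percentage points for objective 1 and, provided 20 are enrolled, under 22 percentage points for objectives 2 to 4.* If the Trial status dates are kept instead, the same wording applies with about 29 eligible and about 24 enrolled at 80% consent. If the rate is per site, both denominators must be reworked.

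The cost is a wording amendment and, if the rate is a total, a less favourable stated precision. No extra patients and no change to the analysis are needed.

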### Recruitment

To achieve adequate participant enrollment, strategies include active screening of eligible patients at each site, clear communication about the study, and collaboration with healthcare providers to identify potential participants. The study team will streamline the consent process, provide educational materials, and hold regular meetings to address recruitment challenges. Recruitment progress will be monitored, and additional outreach efforts will be made as necessary to reach the target sample size.

### Data collection and management

#### Plans for assessment and collection of outcomes

Feasibility objectives will be assessed by tracking the number of neonates approached, enrollment rates, milestone achievement (such as initiation of feeds within 48 h of abdominal closure), and withdrawal rates. Data for the intervention group will be collected prospectively from the electronic health record (EHR) prenatally and through the initial hospital discharge.

#### Plans to promote participant retention and complete follow-up

To promote participant retention and ensure thorough follow-up, the study team will regularly communicate with participants’ families and healthcare providers, and deliver clear details about study procedures. For participants who discontinue or stray from the intervention protocol, essential outcome data—like clinical status, growth metrics, and pertinent hospitalization results—will still be gathered whenever possible. These strategies aim to optimize data completeness and reduce loss to follow-up.

#### Data management

Data for the study will be collected from the EHR and input directly into and stored in REDCap and handled by the research staff at the site. All data will be de-identified.

#### Confidentiality

Personal information about potential and enrolled participants will be collected using secure, study-specific data collection forms and entered into password-protected electronic databases. All study-related information will be stored securely at each site, with physical documents kept in locked files and electronic data protected by access controls. Identifiable information will be accessible only to authorized study personnel and will not be included in any reports, publications, or shared datasets. Data shared outside the study team will be de-identified to protect participant confidentiality. These measures will be maintained before, during, and after the trial to ensure ongoing protection of participant privacy in accordance with regulatory and ethical standards.

### Statistical methods

#### Statistical methods for primary and secondary outcomes

For each feasibility outcome, we will report proportions with 95% confidence intervals. For rate-based outcomes where the denominators can vary by patient (e.g., daily breastfeeding receipt), we will report the overall rate (e.g., the denominator-weighted mean rate). For other binary and continuous outcomes, we will report sample proportions and means, respectively. All estimates will be reported with appropriate 95% confidence intervals.

We will review the data after one subject completes the study, again after five subjects have completed the study, and finally after 10 subjects have completed the study at each of the two sites. We anticipate completion of primary analysis within 3 years.

#### Interim analysis

One interim analysis is planned at the midpoint of participant enrollment to assess safety and feasibility outcomes. The Data Monitoring Committee (DMC) will have exclusive access to interim results and will review recruitment and study data to determine if there are any safety concerns and/or other concerns. The DMC will make recommendations to the study investigators regarding continuation, modification, or termination of the trial based on these findings. Final decisions will be made by the study investigators in consultation with the DMC.

#### Methods for additional analyses, including comparisons to historical controls

We recognize that accounting for specific confounders, such as site, gestational age, birth weight, sex, and race/ethnicity, is important. If feasible, we may consider performing sub-analyses or accounting for these variables in specific models. However, we recognize that our sample size is small and our results most likely will not be generalizable.

For comparisons to historical controls on the study variables described earlier, we anticipate being able to obtain patient-level data from the historical controls, permitting us to use linear and logistic regression to estimate adjusted mean differences or adjusted odds ratios, respectively, with 95% confidence intervals for the current vs. historical control comparisons, adjusting for study site. Continuous outcomes may be log-transformed to improve the validity of the normality assumption, with the Van Elteren test (stratified Wilcoxon Mann–Whitney) used as a backup if parametric tests are not appropriate. If patient-level data from the historical controls is not available but means and/or proportions are available, we will instead estimate stratified means and/or proportions for the current cohort with 95% confidence intervals, permitting comparisons to the historical means and proportions.

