### Management challenges and variability in practice: need for standardization

Despite surgical repair, these neonates often have intestinal dysmotility, resulting in feeding intolerance, prolonged PN courses, and extended hospital stays. On average, neonates with gastroschisis receive their first feed at 15 days of life and require 25 PN days [1, 4, 10]. Management of neonates with gastroschisis varies widely across and within health systems. Clinicians lack evidence-based guidelines, particularly regarding feeding practices [11]. Usual practices in determining timing to start feeds include awaiting return of bowel function which typically consists of a combination of decreasing Replogle output volume, color changing from bilious to clear and/or passing stool. This variability in feeding may contribute to delays in achieving full enteral nutrition and prolong PN exposure and hospitalization.

The University of California Fetal Consortium (UCfC) implemented a standardized pathway (Fig. 1) across eight medical centers. Key advancements include consistent adherence to standardized protocols across institutions, resulting in statistically and clinically significant decreased ventilator days, decreased antibiotic days, and earlier initiation of enteral feeds [12]. While a standardized approach to nutrition improved growth, the duration of PN and length of stay (LOS) remained unchanged [4]. These results reflect unresolved barriers in transitioning to full enteral autonomy.

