### Eligibility criteria

Eligible neonates will have presumed simple gastroschisis born at ≥ 34 weeks of gestation who are hemodynamically stable (not on pressors for blood-pressure support), born to mothers ≥ 16 years old and speak English or Spanish. Simple gastroschisis is defined as gastroschisis without associated intestinal complications—specifically, in the absence of atresia, necrosis, perforation, or volvulus. Deciding whether a neonate has presumed simple gastroschisis is a decision the GAIN study team, comprising of neonatologists and pediatric surgeons, will make in consultation with the primary medical and surgical teams. The pediatric surgeons will inspect the bowel, and the GAIN study team will gather this information and discuss any findings with the primary teams and make a preliminary determination of whether the infant qualifies. Exclusion criteria include complex gastroschisis at time of closure or solidified by definitive operative findings (any ischemic bowel, intestinal perforation, or obvious atresia with mesenteric defect), major congenital anomalies, ionotropic medications, neonates who are wards of the state, futile or redirection of care, participation in another interventional trial, and anyone deemed unfit for participation by study investigators or the primary medical team. A major congenital anomaly is a structural or functional defect present at birth that will have significant impact on the individual, including surgical, medical or serious cosmetic significance [22].

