#### Exploratory outcomes

Data will be collected prospectively via electronic health records. These measures will be compared to a historical cohort using the existing UCFC database, which has been previously approved by IRB protocol # 2216195–2 at UC Davis, and IRB protocol # 24–6179 at UCLA.

Exploratory clinical endpoints will include (1) length of hospitalization (days), (2) time to initiation of feeds from final abdominal closure (days), (3) time to full feeds (100 mL/kg/day or PO ad libitum whichever comes first) from final abdominal closure (hours), (4) duration of parenteral nutrition (days), (5) days of any human milk which includes parent’s own milk and/or donor breast milk during hospitalization, (6) any direct breastfeeding during hospitalization, (7) any direct breastfeeding at discharge (defined as 48 h prior to hospital discharge) (8) any use of parent’s own milk at discharge (defined as 48 h prior to hospital discharge), (9) growth parameters (delta-z-scores for weight and length (discharge–admission measurements).

The length of hospitalization refers to the total number of days spent in the hospital during the initial birth hospitalization. Generally, this will be days in the neonatal intensive care unit (NICU) but can also be days in the pediatric intensive care unit (PICU) or pediatric wards. This will be measured via midnight census data from electronic health records (EHR). Feeding progression covers the initiation of feeds, defined as time to first feed and time to full feeds, both in days. The duration of PN is measured as the number of days of PN. Rates of direct breastfeeding are defined as direct breastfeeding 48 h before discharge. Outcomes of adverse events include rates of necrotizing enterocolitis (> Stage II), sepsis, abdominal compartment syndrome, additional abdominal surgeries (excluding primary closure), and mortality. Medical errors and adverse events will be obtained via solicited reports and review of EHR data.

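### The historical-control comparison commits to adjustment for study site alone and states no eligibility rule for controls, so case-mix differences may look like effects of early feeding

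*Protocol article*

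**What the plan says.** All references are to the protocol article.

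- **Methods for additional analyses, including comparisons to historical controls.** The section opens by saying that "accounting for specific confounders, such as site, gestational age, birth weight, sex, and race/ethnicity, is important". It then makes that adjustment conditional: "If feasible, we may consider performing sub-analyses or accounting for these variables in specific models". The next paragraph specifies the historical comparison as linear and logistic regressions giving adjusted mean differences or odds ratios with 95% intervals, "for the current vs. historical control comparisons, adjusting for study site". If only summary data can be obtained, "we will instead estimate stratified means and/or proportions for the current cohort with 95% confidence intervals", to be set against the historical figures.
- **Exploratory outcomes.** The comparator is given in one sentence: "These measures will be compared to a historical cohort using the existing UCFC database". The section also lists rates of serious complications and death.
- **Eligibility criteria.** "Eligible neonates will have presumed simple gastroschisis born at ≥ 34 weeks of gestation who are hemodynamically stable". Also: "Exclusion criteria include complex gastroschisis at time of closure or solidified by definitive operative findings". Major congenital anomalies and inotropic drugs exclude as well.
- **Trial design.** The trial has a single arm and disclaims efficacy hypotheses.
- **Section on protocol non-adherence and missing data.** Every enrolled infant stays in the primary analysis population, whatever the adherence.

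**The concern.** Two stated features combine. The section names five confounders but commits to one of them, so the other four can be taken up or left out after the data are seen. Trial infants also pass an entry screen that, as far as the article says, the controls do not. Adjusting for site cannot repair this, because simple and complex disease, or term and very preterm birth, differ within a site.

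The likely direction favours the intervention: a screened cohort set against a broader one would show shorter stay, fewer parenteral-nutrition days and fewer complications even if early feeding did nothing. The abstract says that the findings will inform later trials and challenge prolonged bowel rest. In a single-arm study, this comparison is the only comparative evidence on those outcomes.

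A smaller, related weakness is that ordinary logistic regression gives no finite odds ratio when no treated infant has the event.

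**Working it through.** **The plan's own figures.** The article states no figure for the historical comparison. Its only design figures are the error margins for the feasibility proportions, and these reproduce: 1.96 × √(0.25/40) = 15.5 points (stated as under 16) and 1.96 × √(0.25/20) = 21.9 points (stated as under 22). Nothing below alters them.

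**Adjustment set.** Named as important: site, gestational age, birth weight, sex, race/ethnicity. Committed in the regression: site. Optional: the other four.

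**Selection of the two groups.** Trial infants: presumed simple disease, at least 34 weeks, no blood-pressure support, no major anomaly. Controls: the existing database, with no criterion stated.

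**Size of the eligibility component.** Let q_c and q_t be the shares of infants with ineligible-type disease among controls and trial infants, and D their extra days in hospital. If site is unrelated to disease type, the site-adjusted mean difference is biased by

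bias = −(q_c − q_t) × D.

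The documents give none of these three values, so all are assumed. With q_t = 0:

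| q_c | D = 10 | D = 20 | D = 40 | D = 60 |
|---|---|---|---|---|
| 5% | 0.5 | 1.0 | 2.0 | 3.0 |
| 10% | 1.0 | 2.0 | 4.0 | 6.0 |
| 15% | 1.5 | 3.0 | 6.0 | 9.0 |
| 25% | 2.5 | 5.0 | 10.0 | 15.0 |

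(days of stay, in favour of early feeding)

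Setting q_t = 0 gives the largest value in each cell. Trial infants are only presumed simple, and those reclassified later are kept. With q_c = 10%, q_t = 5% and D = 40, the bias is (0.10 − 0.05) × 40 = 2.0 days. With q_c = q_t it is zero.

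**Simulation check.** Linear regression with site as the only covariate, 20 trial infants (the planned enrolment), 100 controls, SD 15 days, true effect zero and q_t = 0. The number of controls and the SD are assumed.

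| q_c, D | Bias, unrestricted | False positives | Bias, restricted | False positives |
|---|---|---|---|---|
| 5%, 20 | −1.0 | 5.4% | −0.03 | 5.1% |
| 10%, 40 | −4.0 | 9.2% | +0.07 | 4.5% |
| 15%, 40 | −6.0 | 17.4% | +0.01 | 4.9% |
| 25%, 40 | −10.0 | 43.3% | +0.04 | 4.2% |

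Restricting controls removes the bias and returns the error rate to about the nominal 5%.

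**Scale.** The Introduction cites 1.9 hospital days per day of feeding delay. A 4-day bias would look like starting feeds 4.0/1.9 = 2.1 days earlier.

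**Zero events.** With 20 treated infants and true rate p, P(no event) = (1 − p)^20. At an assumed 5%: 0.95^20 = 36%. At an assumed 2%: 0.98^20 = 67%. At the 19% sepsis rate in the Introduction: 0.81^20 = 1.5%. The failure is therefore a realistic prospect for rare complications but not for sepsis or the breastfeeding outcomes.

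**The case against.** **The missing filter is an inference from silence.** The article names a data source. It does not describe how controls are chosen, and a condensed article may leave that to the full protocol or analysis plan. A reader might infer that ineligible infants will be included and that bias will follow; the text supports neither. This objection stands, and it limits the point to what may happen. It does not touch the adjustment set, which the article states.

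**Site-only adjustment is not the whole text.** The preceding paragraph allows the other confounders to be modelled if feasible, and with 20 treated infants some caution about covariates is reasonable. This stands in part: site is the only committed covariate, not the only one permitted. Leaving the choice open until the data are in is still the weaker course, and two continuous covariates are affordable for outcomes such as stay.

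**The controls need not come from eight centres.** A reader might take the consortium's reach, "implemented a standardized pathway (Fig. 1) across eight medical centers", as a description of the comparator. It describes where the pathway was used. The database approvals cited are those of the two trial sites, and in a model with site as the only covariate, a centre without trial infants adds nothing to the estimated difference. The eight-centre argument fails.

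**The size is assumed.** This is correct; the figures illustrate and do not estimate. The 1.9-day benchmark is also a slope per day of delay, not the total effect of a multi-day shift in first feeding.

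**The comparison is exploratory.** Also correct. The article adds that the sample is small and the results probably not generalizable. The four feasibility criteria do not depend on this analysis.

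**The backup test.** The Van Elteren test gives a p-value and no interval. That is a minor preference about a fallback and is not pressed here.

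**Conclusion.** The concern holds in limited form. As stated, the historical comparison commits to adjustment for site alone, against the section's own list of important confounders, and no rule requires controls to meet the trial's entry criteria. Case-mix differences may therefore be read as effects of early feeding, most plausibly in its favour.

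The size cannot be determined from the documents. Across assumed differences of 5 to 25 percentage points in ineligible share and 10 to 60 extra days, the shift in mean stay runs from 0.5 to 15 days. It is zero for the eligibility component if the extract is already restricted. Incomplete adjustment for gestational age and birth weight would remain even then, and its size is also unknown.

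The zero-event problem is real for rare binary outcomes, with a probability of 36% at a true rate of 5% and 67% at 2%, both rates being assumed. The documents do not support a claim that bias will occur, or that any feasibility conclusion is at risk.

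**What to change.** 1. **Restrict the controls** to UC Davis and UCLA infants who meet the trial's eligibility criteria as assessed at closure. Final diagnosis should not be used: trial infants later reclassified as complex stay in the analysis, so removing such infants from the controls alone would bias the comparison the other way.
2. **Apply the filter when the data are requested.** If only historical means or proportions are supplied, ineligible infants cannot be taken out afterwards.
3. **Prespecify the covariates:** site, gestational age and birth weight, plus the admission z-score when the outcome is a change in z-score.
4. **Use Firth-penalised logistic regression** when a binary outcome has zero or very few events. Adjustment will be limited there whatever the method, so restricting the controls matters more than adding covariates.
5. **Label all differences from historical controls as descriptive.**

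The cost is a data filter and some analysis wording. The control group becomes smaller and the intervals somewhat wider. Enrolment, the feasibility criteria and their stated margins are unchanged. If the full protocol or analysis plan already contains the filter, the article need only say so.
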